# Methods

## Study design

Household cluster randomized trial of an intensified household contact tracing and treatment support (IHCS) intervention for contacts of both adult and paediatric TB cases.

## Study setting

We will recruit index cases at two South African sites with large differences in annual TB incidence and HIV prevalence Mangaung Municipality (2011 population: 747 431) and the Capricorn Health District in Limpopo (2011 population: 1,293,000) (Stats SA Census 2011 Municipal Fact Sheet) – Figure 1). The antenatal HIV seroprevalence and the annual TB incidence for 2012 in Mangaung and Capricorn Health Districts were 36% and 937/100,000; 30.3% and 686/100,000 and 14.6% and 371/100,000 respectively (Dept of Health, 2013; Health Systems Trust 2013). These two settings will provide valuable information on the intervention when implemented in a TB “hot spot” compared to one with a lower annual TB burden.

Figure 1: Study sites

[figure not shown]

Figure 2. Matlosana municipality and Capricorn district sites

[figure not shown]

[figure not shown]

## Index cases

Using routine reporting of TB cases in health facilities in the two study sites, and lists of specimens positive for TB generated by routine public sector laboratories in the two study sites, the recruiting teams will identify potentially eligible patients in clinics and hospitals. Once a potential index patient has been identified, if it appears they currently reside permanently within the boundaries of one of the study sites, they will be approached and invited to participate in the the study. Following the informed consent process, we will recruit consecutive index TB patients (those 7 years and older with pulmonary TB, and children under 7 years with TB of any organ) diagnosed with TB and currently residing in the catchment health facilities in each of the study sites. If older index cases (7 years and older) are extremely ill and are unable to provide their own assent or informed consent, we will obtain proxy consent from next-of-kin. Moreover, using sensitive approaches we will also attempt to obtain consent from next of kin of potential index cases who died soon after their diagnosis of TB.

**Inclusion Criteria for Index Cases**

1. Any patient (living or recently deceased) diagnosed with TB at any health facility in the study districts in the six weeks prior to recruitment.
   1. For index cases with TB older than 7 years of age, laboratory confirmation of **pulmonary TB disease** is required, evidenced by hard copy lab report of at least one of: a smear positive result for acid fast bacilli (graded as +, ++, or +++); an Xpert MTB/Rif test or other WHO recommended molecular assay positive for *M. tuberculosis*; a mycobacterial culture positively identified as *M tuberculosis*; or a histology/cytology report from a biopsy that includes lung tissue that is suggestive of TB disease. LF-LAM may be used to assist in the diagnosis of TB in HIV positive patients with signs and symptoms of TB (pulmonary and/or extrapulmonary) who have a CD4 cell count less than or equal to 100 cells/μL, or HIV positive patients who are seriously ill regardless of CD4 count or with unknown CD4 count. Evidence of a hard copy of recorded LF-LAM result is required.
2. For index cases 7 years and younger, the diagnosis of **TB of any organ** will be evidenced by – at a minimum- firstly: a recorded diagnosis of TB and its anatomical site in any clinic or hospital record; and secondly the prescription of multidrug TB treatment by a doctor for a child with signs and symptoms suggestive of TB. The presence of signs or symptoms suggestive of TB may be obtained either from the clinical record or from the caregiver.
3. Permanent resident in a household with at least one other person in either the Capricorn Health District or the Matlosana Municipality for a total of at least three months in the six months prior to recruitment.
4. Either the participant, the parent or next of kin of a participant declare they have no plans for relocation of their household to another municipality or health district during the course of follow up.

**Exclusion Criteria for Index Cases**

1. The research team is unable to obtain informed consent or assent for the following reasons:
   1. Participant is unwilling to provide informed consent or assent;
   2. The research team is unable to obtain informed consent from the parents of participants younger than 18 years;
   3. The research team is unable to obtain consent for participation from the close next-of-kin of adult patients who are too ill to provide their own consent, or have died.
2. Patients with TB who appeared to have developed or contracted TB or while either institutionalized or incarcerated. Similarly, no person incarcerated or institutionalized at the time of diagnosis will be included in the study.
3. If the study team is unable to locate the household of the index case, or if there is no other household member/s able to be recruited at the household, the participant will be withdrawn from the study.

## Index case identification and consent procedures

A team of enrolled nurses will recruit index cases. They will be equipped and trained to use N95 or other appropriate respiratory protection and infection control measures and also in Good Clinical Practice. They will visit hospitals, clinics and TB laboratories in the catchment areas of the study on repetitive, frequent cycles, to identify potential index cases diagnosed in the past six weeks. Index cases and the parents of index cases younger than 18 will be approached to obtain consent for their own participation in the case of index cases; and in the case of parents of an index case, consent for participation of their child in research Using sensitive approaches, we will attempt to obtain consent from the close next-of-kin of patients with TB who died in hospital/ or at home. Deceased patients who were diagnosed with TB will only be enrolled into the study if date of death is no more than 6 weeks from date of enrolment. If a potential index case of any age is too unwell to comprehend the informed consent process, the research team will approach close next-of-kin of the patient with TB and ascertain if they would give consent for the participation of the index case and his/her household in the study. For this study close next-of-kin are: current spouse living together for past year in the same household, sibling older than 25 years of age, biological parent or biological grandparent – the latter if parents are not available or have passed away.

Adults sputum positive for acid fast bacilli, or with a cycle threshold (Ct) on Xpert MTB/Rif of ≤24, and those with drug resistant TB will take precedence for recruitment, in the event the study capacity to recruit eligible households is exceeded.

Enrolled nurses will provide prospective participants with verbal and written information about the study, emphasising the procedures involved in the study, especially that the study involves a study visit to the household. They will be informed that household members will be asked questions about the health, testing and treatment, and also about other issues such as costs of health care and illness. Following provision of information and answering any questions, individuals will be invited to provide informed consent to participate in the language of their choice, with consent recorded by signature on a study consent form. Parental consent to participate in research will be obtained for children <18 and assent will be obtained from children 7-14 years. Individuals who are illiterate, or unable to write, will be invited to provide a thumbprint confirmation of consent to participant, accompanied by a witness signature.

Potential participants, their parents, or their next of kin will be informed that non-participation will have no detrimental effect on the care they will continue to receive and that no incentives (financial or otherwise) will be provided to any study subject.

## Procedures for all index case TB participants

After obtaining informed consent, enrolled nurses will administer a baseline index case demographic and clinical questionnaire (including presence and duration of symptoms, comorbid conditions, treatment received and laboratory confirmation of TB). Additionally, the study staff will obtain from each index case a handwritten household census comprising the first two letters of the first name and first two letters of the last name and ages and genders of all of their household members.

Index TB cases will continue to receive TB treatment and HIV testing and care through routine clinical services according to South African National Guidelines. Results of routine TB and HIV investigations completed by the health facility (sputum smear, sputum TB culture, Xpert MTB/Rif, HIV-test, CD4 count, HIV viral load), TB category (pulmonary, extra-pulmonary); and treatment initiation dates will be extracted from clinical records and recorded by study staff using data extraction forms).

This is an open study and we cannot blind index cases, their households, or study field research teams to allocation. However, investigator blinding will be maintained until final analysis – no interim analyses which reveal results of the study or provide an indication by group lab results or other outcomes will be provided to site staff or an investigator (apart from the trial statistician). The trial will be unblinded by the trial statistician only to the closed part of the data safety management board (DSMB) meetings, on completion of all trial activities and data cleaning, or if there is agreement to prematurely halt the study because of safety, or other participant or health service concerns, futility, or because the trial overall objective has been met prior to full recruitment or follow up.

# Trial Procedures

**Intervention group (**intensified household contact tracing and treatment support [IHCS]):

*Intensified contact tracing & baseline assessment*
A team comprised of an enrolled nurse and two counsellors will conduct household visits with supervision by a research nurse. An experienced study coordinator at each site will take overall day-to-day management of recruitment and follow up at each site.

**The initial household contact** will be conducted within 14 days of recruitment of each index case allocated to the intervention group. Following provision of information and permission from household head, a brief household survey will be done to assess household poverty status and dwelling characteristics, including tallying windows, external doors and rooms.

During the first household contacts which we will limit to three visits at different times of the day and week to accrue as many household members as possible. Before any individual level data is collected, Research Assistants will obtain individual written informed consent to participate from each household member over 14 years; parental consent for children <18 years to participate in research, and assent from those aged 7 years to 14 years old. We will administer a short questionnaire to each recruited household member that includes: demographic details including relationship and airspace sharing with the recruited index case; risk factors for TB; presence of TB symptoms; and history of previous and current HIV and TB treatment; current quality of life; and employment status and income

In addition, we will question the household head/s about the cost of the index case TB and diagnosis has had on the household. We will attempt to ascertain costs, from the patient household perspective, of a TB diagnosis. If the index case has passed away, the costs related to the funeral and final burial of the body will be ascertained. We will also ascertain the contribution of the ill or deceased person to the total household income. This will be done in a sensitive manner, with interviewers having been trained in grief counselling and aware of changes in emotion of the interviewee, being able to terminate the interview if required. Participants either requesting additional assistance or being seen to require additional assistance will be referred to appropriate care or social assistance.

**Sputum Collection**

To avoid bias related to collecting better quality sputum samples from symptomatic patients, we will collect one spot sputum sample from all household members capable of producing a sputum sample, before we ask about TB symptoms. Prior to producing a sputum specimen household members will be asked to drink a cup of water and rinse out their mouths, then take four deep breaths prior to giving a good cough effort. If small volumes of sputum are obtained, we will allow up to three hours for the collection of a spot sputum specimen. This specimen will be subjected to Xpert MTB/Rif (or the at time-of-study current version of the usual first line TB lab test in the public sector) and liquid mycobacterial culture at public sector laboratories. Single sputum specimens will be at least 3ml and at the lab will be mixed with decontaminant as per standard operating procedures in the two public sector laboratories we will send specimens to - then split into two: Xpert MTB Rif (with subsequent addition of buffer) and immediate liquid culture in the MGIT automated system as per current protocols in public sector mycobacterial laboratories. We will record the cycle threshold number of the Xpert and the time-to-positive in liquid culture. Sputum samples will be immediately stored and transported in coolboxes at 4ºC to public sector laboratories for testing. Anyone who tests positive for *M tuberculosis* will be immediately referred to their chosen public sector clinic for TB treatment initiation with a clear referral letter. For those who are Xpert MTB/Rif negative, HIV-negative and over 5 years of age a tuberculin skin test will be performed with the needle of the syringe parallel to the long axis of the arm at this initial visit and read 48 – 72 hours later using the ball-point pen to mark the widest transverse diameter measured with the reverse calliper method in millimetres. No induration will be documented as 0mm.

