**HIV testing**

All household members will be offered HIV testing after counselling, in the first instance using a serial rapid diagnostic test algorithm, the kits for which will be provided provided by the Provincial Departments of Health. Research Assistants trained and accredited in HIV testing and counselling. In line with recommendations in the World Health Organization’s HIV Testing Services Guidelines 2015, a negative A1 test result will diagnose participants as HIV-negative. Positive results to both Tests A1 and the confirmatory A2 test will diagnose participants as HIV-positive. Where results to Test A1 and A2 are discrepant, both tests will be repeated, and followed by a tie-breaker using a laboratory-based 4^th^ Generation ELISA (anticipated in <1 per 1000 participants). Couples testing will be provided if requested.

Children under 18 months of age will have a dried blood spot sample taken for HIV PCR testing as per South African National Guidelines, with testing performed at the National Institute for Communicable Diseases. Results-based post-test counselling will be offered individually in a private setting out-of-earshot and out of sight of other household members.

Participants declining HIV testing may be offered alternative laboratory-based HIV testing on either a blood specimen or an oral fluid specimen using OraQuick, OraSure Technologies –depending on their availability, with communication of results within one week, but if still reluctant to be HIV tested, will be asked to provide an anonymous oral fluid sample for HIV testing for study purposes. Those who request anonymous testing without receipt of results and those who refuse HIV testing will be encouraged to go to a HIV testing facility for testing.

All participants who test HIV positive will be referred to their nearest clinic for initiation of ART. We will draw blood specimen for CD4 count estimates -if still required by National Guidelines as these are expected to change to a test and treat approach in the near future – as soon as the participant is diagnosed with HIV. Participants who test HIV positive will receive supported access to HIV treatment, prearranged by the study at their nearest HIV care clinic.

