**Follow-up household visit (1week after baseline household visit)**
Xpert MTB results and results of laboratory HIV testing (and CD4 counts and HbA1C as appropriate) will be communicated to participants by study staff including registered nurses at a follow-up household visit approximately one-week after the baseline assessment is completed. Participants with microbiologically-confirmed tuberculosis or diagnosed with HIV will be supported to attend their nearest local primary care clinic to register for ongoing care and treatment.

Participants who are older than 5 years of age or test HIV-negative and whose sputum tests are negative for TB and whose tuberculin skin test is negative will be dispensed the first month of IPT by study nurse and then referred for ongoing preventive treatment at their local clinics with a clear referral letter that includes all results. Additionally all those participants who are less than 5 years of age or are HIV-positive and sputum tests are negative for TB will be dispensed the first month of isoniazid preventive therapy by study nurses, Linkage to care will be confirmed by collection of referral cards at study facilities by study staff. Home tracing to encourage re-entry to care will be undertaken on three occasions for participants who do not attend clinics within 2 weeks of referral.

Should any liquid TB culture be resulted positive after this visit, a visit will be made to the few anticipated households from where this result was taken to inform the patient and refer him/her for TB treatment.

| **Age of household member** | **HIV status** | **TST Required** | **Active TB disease** | **TB HH contact** | **IPT initiated** | **Study procedure** |
| --- | --- | --- | --- | --- | --- | --- |
| Child < 5 years | POSITIVE on ART or not | NO | NO | YES | YES | Initiate 1 month IPT |
| Child ≥5 years, adult or adolescent | POSITIVE on ART or not | NO | NO | YES | YES | Initiate 1 month IPT |
| Child < 5 years | NEG | NO | NO | YES | YES | Initiate 1 month IPT |
| Child ≥5 years, adult or adolescent | NEG | YES | NO | YES | YES | Initiate 1 month IPT |

Table 1. IPT initiation for household contacts without TB symptoms

*Final intervention household visit (3 months after baseline household visit)*

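### The baseline skin test requires a negative Xpert result but is scheduled at the visit where the sputum for that Xpert is only being collected

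*Protocol*

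**What the plan says.** Under Sputum Collection, the protocol collects one spot sputum from each contact able to give one and sends it in coolboxes "to public sector laboratories for testing", where it is split for Xpert and liquid culture. The same paragraph then sets both the condition and the timing of the baseline tuberculin skin test. The condition is: "For those who are Xpert MTB/Rif negative, HIV-negative and over 5 years of age a tuberculin skin test will be performed". The timing is "at this initial visit and read 48 – 72 hours later".

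Under the follow-up household visit heading, Xpert results "will be communicated to participants by study staff including registered nurses at a follow-up household visit approximately one-week after the baseline assessment is completed". At that visit the first month of isoniazid is dispensed. For the older HIV-negative group the decision uses both the sputum result and the skin test; Table 1 marks the skin test as required only for that group. Contacts under 5 or HIV-positive are decided without it.

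Under HIV testing, rapid testing comes first, and "a negative A1 test result will diagnose participants as HIV-negative", so this part of the condition can be settled on the day. Contacts who decline the rapid test may have a laboratory or oral-fluid test instead, "with communication of results within one week".

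**The concern.** The skin test depends on a result that, on the protocol's own schedule, does not yet exist when the test is due. Taken literally, no contact is known to be Xpert-negative at the initial visit, so no contact qualifies. Field staff have to depart from one half of the rule, and the protocol does not say which half.

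Preventive therapy guided by the skin test is the third listed component of the intervention in the Executive Summary. The first of the secondary objectives concerns isoniazid in HIV-seronegative, skin-test-positive people. Both need the test to be placed and read in a consistent way. If teams settled the conflict differently, the delivered intervention could differ between districts. The protocol does not show that this will happen, but it does nothing to prevent it.

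**Working it through.** The plan gives no figure for this point. The check is a day count from its own intervals.

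**Inputs**
- Day 0: initial visit, sputum collected (Sputum Collection).
- Reading = placement + 2 to 3 days (48–72 hours, Sputum Collection).
- Dispensing visit: about day 7, counted from completion of the baseline assessment (follow-up household visit).
- Next scheduled household visit: about 3 months after the initial assessment (final intervention household visit).
- Laboratory turnaround for Xpert: not stated.

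**Three ways to act on the text**

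| | Placement | Reading | Against the day-7 visit |
| --- | --- | --- | --- |
| (a) Keep the timing, set aside the Xpert condition | day 0 | 0 + 2 to 3 = day 2–3 | 7 − 3 to 7 − 2 = 4 to 5 days before |
| (b) Keep the condition, wait for the one-week visit | day 7 | 7 + 2 to 3 = day 9–10 | 2 to 3 days after |
| (c) Get Xpert early, place between visits | by day 7 − 3 to 7 − 2 = day 4–5 | by day 7 | just in time |

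Course (a) departs from the written eligibility condition. Course (b) departs from the written placement visit and leaves no reading at the visit where it is used. Course (c) also departs from the written placement visit. It assumes a laboratory result within about 4 to 5 days and a placement contact that the protocol does not name.

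**Does a spread-out baseline change this?** The initial contact may take up to three visits. If baseline is completed on day c, the one-week visit falls on day c + 7. A test placed then is read on day c + 9 to c + 10, still 2 to 3 days late. The ordering in (b) does not depend on c.

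**HIV condition.** With the rapid test, status is known on day 0 and there is no conflict. With the laboratory or oral-fluid alternative, the result may come as late as day 7. A test held for it would then be read as late as day 9–10, as in (b).

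**Contacts per household.** Course (a) needs three: day 0, reading on day 2–3, dispensing on day 7. Course (b), with dispensing at the reading if the clinicians so chose, also needs three: day 0, placing on day 7, reading on day 9–10. A separate reading contact is needed either way.

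**The case against.** The strongest reply is that the schedule works if the stated visit is kept. The reading is then available 4 to 5 days before dispensing, and the follow-up section separately requires negative sputum tests at that point, so the sputum check is not lost. This stands. A reader might infer that the isoniazid decision has no skin test result to rest on. That is true only if staff wait for Xpert until the one-week visit, and the protocol does not tell them to.

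A second reply is that the follow-up section fixes when participants hear their results, not when staff receive them, and that people who test positive are to be referred at once. An earlier result is therefore possible. This stands in part: it keeps course (c) open, but a result that arrives later still does not make anyone known to be Xpert-negative at the initial visit.

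A third reply points to "During the first household contacts which we will limit to three visits at different times of the day and week". Those visits are meant to reach more household members. Nothing says that staff return with results and place skin tests then.

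A fourth reply is that the three-month visit helps contacts who have not taken up isoniazid to start it. This limits any loss under course (b), but does not remove the conflict.

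A reader might also infer that every intervention household would need an extra visit. The count of contacts above does not support this: waiting moves the reading visit and does not in itself add one.

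**Conclusion.** The point holds as a contradiction between a condition and its timing: the Xpert condition for the baseline skin test cannot be met at the visit where the test is scheduled. Keeping the timing gives a reading on day 2–3, in time for the one-week visit. Waiting for Xpert until that visit gives a reading on day 9–10, too late for it, with the next scheduled household visit at about three months. The day counts take the one-week visit as day 7 and assume nothing about laboratory turnaround except in course (c).

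The conflict affects HIV-negative contacts over 5 in the intervention arm. The protocol gives a planned 2,400 index cases and a mean household size of 5.5, but not the share of contacts who are HIV-negative and over 5, so no number can be put on the group. The HIV part of the conflict covers only those who decline rapid testing, also an unstated number.

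The weight is moderate. Delivery of one intervention component, and a secondary objective that rests on it, are exposed. The primary analysis is not invalidated.

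**What to change.** Reconcile the Sputum Collection and follow-up visit sections so that three things hold together: the condition for placing the skin test can be checked at the visit where it is placed; that visit is named; and the reading is available when the follow-up section uses it. State also what applies to contacts whose HIV result comes later than the initial visit. The sponsor's clinicians decide how; this review does not propose a clinical rule.

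While those sections are open, note a separate conflict. The follow-up text links isoniazid in the older HIV-negative group to a negative skin test, whereas the Executive Summary names contacts with a positive one. These passages must be reconciled too.

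The cost is a short protocol amendment and matching field instructions. If the sponsor chooses to re-time a visit, the visit schedule has to be updated as well.
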